### Participants

The eligibility criteria will be: Inclusion–(I) rearfoot striking runners with cadence under 170 steps/minute; (II) age between 18 and 45 years; (III) pain around or behind the patella, with intensity of at least 3/10 on the Visual Analogue Scale (VAS), during running and one task among squatting, climbing, and descending steps, kneeling and extending the knee with resistance [24]; (IV) being comfortable running at a speed of 10–12 km/hour. Exclusion—(I) Other disorders in the lower limbs; (II) history of surgery in the lower limbs in the last year; (III) not showing interest to adhere to a strict running retraining protocol for 2 weeks. Participants with unilateral or bilateral symptoms will be included, however, in the second case, only the worst knee (pain intensity) will be considered for analysis. The participants will be recruited through contact via e-mail, telephone, and through personnel with Goiânia’s running clubs in search of runners with PFP. In this first contact, general (gender, age, body mass, height, body mass index, history of injury and previous surgeries in the lower limbs), running (experience, volume, frequency) and pain information (intensity, location, duration of symptoms and functional tasks related to pain) will be assessed to see if the participants are eligible. Based on pain information, the diagnostic will be established using the following criteria: pain around or behind the patella during functional activities that loads the patellofemoral joint [24]. A systematic review of reviews concluded that anterior knee pain produced by functional tasks is currently the best diagnostic indicator of PFP [25]. Also, PFP is evident in 80% of the people who present anterior knee pain during a squatting manoeuvre [26].

Ethics approval was obtained from the Institutional Review Board of University of Brasilia/Faculty of Ceilândia (4.132.491), and all subjects will sign a detailed consent form before entering the study (S2–S4 Files). This study was registered in the Brazilian Registry of Clinical Trials (RBR-8yb47v) (S6 File).

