### Data analysis

The data of each participant will be extracted for SPSS (Statistical Package for Social Sciences) version 23.0 for later statistical analysis. Descriptive analysis will be performed with calculation of means, standard deviations and 95% confidence intervals for quantitative variables and frequencies and percentages for qualitative variables. Data normality and sphericity will be tested using the Shapiro-Wilk and Mauchly’s tests, respectively. Baseline demographic data will be compared using ANOVA (parametric data), Kruskall-Wallis (non-parametric data) and Chi-squared tests. To compare the effects of the rehabilitation programs on the outcomes of the study, a repeated measures ANOVA with a 3-by-3 mixed-model (parametric data) or the Generalized Estimation Equations procedure with gamma distribution model (non-parametric data) will be used. Time (t0 x t2 x t24) will be used as repeated factor, group (impact x cadence x control) as independent factor and the mean of points on the visual analog pain scale, mean of points on the Patellofemoral Disorders Scale, and the peak in degrees of the contralateral pelvic drop, hip adduction, ankle dorsiflexion and knee flexion during midstance, and foot inclination and tibia inclination during initial contact as dependent variables. Baseline characteristics that are different across groups will be included as covariates in the model. Significance level of p <0.05 will be adopted. Sidak’s post-hoc will be used to make pairwise comparisons. Subgroup analysis and adjusted analysis will not be performed. Intention-to-treat analyses will be conducted where the subjects will be analyzed independently of adherence to the protocol or retention in the follow-up.

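### Covariates are to be chosen by baseline difference, yet adjusted analysis is ruled out three sentences later, which leaves the primary model undetermined

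*Protocol article*

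**What the plan says.** All the relevant text is in the protocol article, mostly under Data analysis.

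- Baseline testing: "Baseline demographic data will be compared using ANOVA (parametric data), Kruskall-Wallis (non-parametric data) and Chi-squared tests".
- Main comparison for every outcome: "a repeated measures ANOVA with a 3-by-3 mixed-model (parametric data) or the Generalized Estimation Equations procedure with gamma distribution model (non-parametric data) will be used". The repeated factor is time, with levels t0, t2 and t24, and the independent factor is group.
- Covariates in that model: "Baseline characteristics that are different across groups will be included as covariates in the model".
- The next two sentences give the threshold, "Significance level of p <0.05 will be adopted", and the Sidak post-hoc procedure.
- Then: "Subgroup analysis and adjusted analysis will not be performed".

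No covariate is named. The section does not define what counts as a difference; the baseline tests and the general 0.05 level are the only means it offers.

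**The concern.** A model that contains baseline covariates is an adjusted analysis. Read plainly, one sentence requires adjustment of the main model and the other forbids it, and nothing says which prevails. The analyst would have to decide with the data at hand.

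The covariate rule is also weak taken alone. Under proper randomisation every baseline difference is a chance difference, and a significance test on it does not show whether the variable predicts pain. The article's Discussion links longer symptom duration and worse function to a poor prognosis. Under the stated rule those variables would enter only if they happened to be unbalanced, and height would enter on the same terms.

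At stake is whether the primary estimate is adjusted, for what, and with what precision.

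**Working it through.** **The plan's own figure.** Sample size gives partial eta squared 0.19, f = 0.48, alpha 0.05, power 99%, 3 groups and 3 measurements, leading to 21 participants.

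- f = √(0.19/0.81) = 0.484.
- With the unstated settings assumed to be correlation 0.5 and sphericity 1, λ = f²·N·m/(1−ρ) = 0.48² × 21 × 3/0.5 = 29.0, on (3−1)(3−1) = 4 and (21−3)(3−1) = 36 degrees of freedom.
- Power is 99.04% at N = 21 and 97.3% at N = 18, so 21 is reproduced. The planned total of 30 equals 21/0.70, or 10 per arm at 1:1:1.

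This calculation has no covariates, so the conflict does not change the stated N.

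**How often chance would select a covariate.** The candidate items come from Participants: "general (gender, age, body mass, height, body mass index, history of injury and previous surgeries in the lower limbs" (7 items) and "running (experience, volume, frequency) and pain information (intensity, location, duration of symptoms and functional tasks related to pain" (3 running and 4 pain items), 14 in all. Assume independent tests, each at exactly 0.05. The chance of at least one difference is 1 − 0.95^k:

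| Items tested | k | Chance of at least one |
|---|---|---|
| Gender, age, body mass, height, BMI | 5 | 22.6% |
| All general items | 7 | 30.2% |
| All listed items | 14 | 51.2% |

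With 14 items, 14 × 0.05 = 0.7 covariates are selected on average. Body mass, height and BMI are correlated, so the true figures are somewhat lower.

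**What the rule does to the test.** A simplified simulation used 10 per arm, 14 independent normal baseline variables, one of them prognostic, a single outcome time and 5,000 trials per setting. Correlation r between the prognostic variable and the outcome is assumed.

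| Setting | Never adjust | Adjust by baseline difference | Better of the two | Opposite verdicts |
|---|---|---|---|---|
| No effect, r = 0.3 | 5.1% | 4.8% | 5.8% | 1.7% |
| No effect, r = 0.5 | 4.6% | 4.0% | 5.5% | 2.5% |
| No effect, r = 0.7 | 4.3% | 3.4% | 5.1% | 2.5% |
| Effect 1.2 SD in both active arms, r = 0.5 | 73.9% | 70.5% | 75.6% | 6.9% |
| Effect 1.2 SD in both active arms, r = 0.7 | 75.5% | 72.2% | 77.8% | 8.0% |

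The first three result columns are the share of trials significant at 0.05. In the two effect settings, fixing the prognostic variable in advance gave power of 84.3% and 95.9%. Those two figures compare with a single-time unadjusted analysis. They are not the gain over the planned model, which already uses t0.

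**Gain from t0 as a covariate.** Relative to change from t0, with equal variances at both times, the variance ratio is (1−ρ²)/[2(1−ρ)] = (1+ρ)/2. This gives 0.65, 0.75 and 0.85 at assumed ρ of 0.3, 0.5 and 0.7, that is 35%, 25% and 15% less variance.

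**The case against.** **The second sentence may mean something milder.** Paired with subgroup analysis, it could exclude only analyses additional to the main model. The text does not say so, but the reading is possible, so a reader should not treat the contradiction as beyond argument. That reading leaves selection by chance imbalance untouched.

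**The baseline score is not ignored.** A reader might infer that the outcome's own baseline is left out unless it happens to differ. It is not: t0 is a level of the time factor, so the group-by-time interaction already uses it. What stands is narrower: change-type use of t0 is less efficient than covariate adjustment, by an amount that depends on a correlation the article does not give.

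**The 51% figure is the upper end.** The 14 items are collected to judge eligibility and are not declared as candidate covariates, and the tests are specified for baseline demographic data only. The lower figures of 23% and 30% are at least as defensible.

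**The analyst is blinded.** Randomisation/Blinding says that the researcher analysing the data will not know the assigned group. This limits deliberate selection, but it does not tell that researcher which sentence to follow.

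**Conclusion.** The concern holds as a conflict between two statements about the same model, together with a covariate rule driven by chance imbalance. The article does not settle whether the primary analysis is adjusted or for what. Under the covariate rule, chance alone would bring in at least one covariate in roughly 23% to 51% of trials, depending on which items are tested and assuming independence and a 0.05 threshold.

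The consequence is an undetermined primary model and lost precision. In the simulation the data-driven rule had about 3 points less power than never adjusting, and the two rules disagreed on significance in 7% to 8% of trials with an effect.

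A reader might infer serious inflation of type I error. The figures do not support that: applied mechanically the rule is slightly conservative (3.4% to 4.8%), and taking the better of the two rules reaches only 5.1% to 5.8%. These results rest on the simplified simulation and its assumed correlations and effect.

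**What to change.** 1. Delete the sentence on covariates chosen by baseline difference, and do not use baseline tests to select covariates. Whether to report such tests descriptively is a separate matter.
2. Put in its place: *Each outcome model includes the t0 value of that outcome as the only covariate, fixed in advance whatever the baseline differences, with t2 and t24 as the repeated outcome levels.* The last clause is needed so that t0 is not both outcome and covariate.
3. Reword the later sentence so that the restriction on subgroups survives: *No subgroup analyses and no adjusted analyses beyond this model will be performed.*

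No new data are needed, since t0 values are already collected. The covariate costs one degree of freedom between participants (with 30 analysed, 30 − 3 = 27 becomes 26). The design becomes 3-by-2, and the treatment comparison becomes the group contrasts at t2 and t24. The Sample size section should therefore note that its calculation (three measurements, within-between interaction) rests on the 3-by-3 model.

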## Abstract

Patellofemoral pain (PFP) is one of the most prevalent injuries in runners. Unfortunately, a substantial part of injured athletes do not recover fully from PFP in the long-term. Although previous studies have shown positive effects of gait retraining in this condition, retraining protocols often lack clinical applicability because they are time-consuming, costly for patients and require a treadmill. The primary objective of this study will be to compare the effects of two different two-week partially supervised gait retraining programs, with a control intervention; on pain, function and lower limb kinematics of runners with PFP. It will be a single-blind randomized clinical trial with six-month follow-up. The study will be composed of three groups: a group focusing on impact (group A), a group focusing on cadence (group B), and a control group that will not perform any intervention (group C). The primary outcome measure will be pain assessed using the Visual Analog Pain scale during running. Secondary outcomes will include pain during daily activities (usual), symptoms assessed using the Patellofemoral Disorders Scale and lower limb running kinematics in the frontal (contralateral pelvic drop; hip adduction) and sagittal planes (foot inclination; tibia inclination; ankle dorsiflexion; knee flexion) assessed using the MyoResearch 3.14—MyoVideo (Noraxon U.S.A. Inc.). The study outcomes will be evaluated before (t0), immediately after (t2), and six months (t24) after starting the protocol. Our hypothesis is that both partially supervised gait retraining programs will be more effective in reducing pain, improving symptoms, and modifying lower limb kinematics during running compared with the control group, and that the positive effects from these programs will persist for six months. Also, we believe that one gait retraining group will not be superior to the other. Results from this study will help improve care in runners with PFP, while maximizing clinical applicability as well as time and cost-effectiveness.

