
Unfortunately, the main gait retraining protocols are not feasible in clinical practice, since they consume a lot of time and financial resources for patients [11,23]. In fact, a recent study showed positive effects after a single session of cadence retraining on symptoms and biomechanics of runners with PFP [16]. Therefore, we chose to compare two partially supervised running retraining programs, one group focusing on impact and another group focusing on cadence.

The primary objective of the study will be to compare the effects of two different two-week partially supervised gait retraining programs, one focusing on impact and the other focusing on cadence, with a control intervention; on pain, function and lower limb kinematics of runners with PFP. The secondary objective of the study will be to compare the effects of these programs on pain, function and lower limb kinematics six months after their application.

Gait retraining with focus on impact has been proved to modify the ground reaction forces in pain free-subjects (tibial acceleration, vertical impact peak, instantaneous and average loading rates) [20–22], while the gait retraining with focus on cadence has been proved to modify symptoms, kinematic (increased hip adduction, contralateral pelvic drop and knee flexion) and kinetic aspects (patellofemoral loading rate) in patellofemoral pain patients [15,16]. Our hypothesis is that the two partially supervised gait retraining programs will be more effective in reducing pain, improving symptoms, and modifying lower limb kinematics during running compared with the control group, and that the positive effects from these programs will persist for six months. It is expected a reduction in contralateral pelvic drop, hip adduction, knee flexion, ankle dorsiflexion, tibia and foot inclination in both retraining groups. Also, we believe that one gait retraining group will not be superior to the other. The main motivations to perform a comparison of partially supervised gait retraining programs are the lack of clinical trials and the possibility to provide viable options for runners with PFP.

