### Outcomes measures (dependent variables)

The primary outcome of the study will be: (I) pain during daily activities (usual)—assessed using the Visual Analog Pain Scale [29]; The secondary outcomes will be: (II) pain during running—assessed using the Visual Analog Pain Scale [29]; (III) function—assessed using the Patellofemoral Disorders Scale [31]; (IV) kinematics of the lower limbs in the frontal (contralateral pelvic drop; hip adduction) [33,35,36] and sagittal planes (foot inclination; tibia inclination; ankle dorsiflexion; knee flexion) [33,37,38]–assessed through digital videos using two webcams (MyoVideo 139 HD Color Webcam) sampling at 30 frames per second and two leds (LED Floodlight) [33]. The video recordings will be analyzed using the MyoResearch 3.14 –MyoVideo software (Noraxon U.S.A. Inc.). The kinematic variables of interest were chosen based on previous studies [14,15,19,47,48]. The systematic review and meta-analysis of Neal and colleagues [14] shows a relationship between increased hip adduction and contralateral pelvic drop with PFP. The study of Wille and colleagues [47] showed that foot inclination angle and peak of knee flexion are variables that may predict knee joint loading and PFJ forces during running. Tibia inclination during initial contact is related with cadence and length [48] and these are associated with PFJ forces [18,19]. For the comparison of the three study subgroups, the average of points on the visual analog scale of pain, average of points on the scale of Patellofemoral disorders and the peak in degrees of the contralateral pelvic drop, hip adduction, knee flexion and ankle dorsiflexion during midstance and foot inclination and tibia inclination during the initial contact will be considered. The three groups will be compared before (t0), immediately after (t2) and six months (t24) after starting the protocol.

Regarding the retention of the participants, to ensure that there are minimal losses during the follow-up period, the researchers will make a monthly phone call to monitor pain, the current level of training, physical activity practice and if the participants sought for other methods of treatment. Participants can withdraw from the study for any reason at any time, in which case the researchers will collect the pain and function outcomes using the aforementioned instruments (if possible) and report the reasons why these patients did not complete the follow-up (Fig 1).

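### Function and six joint angles are labelled secondary yet sit inside the primary objective, and all nine outcomes are tested at 0.05 with no testing order, cross-outcome adjustment or supportive label

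*Protocol article*

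**What the plan says.** All places are in the protocol article.

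- **Data analysis.** A three-group by three-visit model, or a GEE alternative for non-normal data, is fitted to each dependent variable. The error-control rule is: "Significance level of p <0.05 will be adopted. Sidak’s post-hoc will be used to make pairwise comparisons". No order of testing, adjustment across outcomes, or supportive or exploratory label is given.
- **Outcomes measures.** One primary outcome is named: "The primary outcome of the study will be: (I) pain during daily activities (usual". Running pain, function ("III) function—assessed using the Patellofemoral Disorders Scale") and the kinematic angles, two frontal and four sagittal, are secondary.
- **Abstract.** It also names one primary outcome, but the other pain score: "The primary outcome measure will be pain assessed using the Visual Analog Pain scale during running". Function and kinematics are again secondary.
- **Introduction.** The primary objective compares the two programs "with a control intervention; on pain, function and lower limb kinematics of runners with PFP"; the Abstract repeats this. The hypothesis adds: "It is expected a reduction in contralateral pelvic drop, hip adduction, knee flexion, ankle dorsiflexion, tibia and foot inclination in both retraining groups".

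**The concern.** Two parts of the document pull apart. The outcome labels put function and kinematics below a single pain outcome. The objective and hypothesis put them alongside pain, with a predicted direction for each angle. The analysis section does not settle which reading governs, because it holds every outcome to the same 0.05 and confines its multiplicity method to pairs.

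At stake is what a single positive result may be taken to show. The trial randomises 30 runners, about 10 per arm, and was sized on knee pain only. One angle or score crossing 0.05 by chance is quite likely, and under the stated primary objective it could be presented as support for the main hypothesis.

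**Working it through.** **1. The plan's own figure.** The article states no error rate across outcomes. Its only related calculation is the sample size, based on the group-by-time interaction for knee pain.
- Effect size: f = √(0.19/0.81) = 0.484, stated as 0.48.
- Noncentrality: λ = f²·N·m/(1−ρ) = 0.2304 × 21 × 3 / 0.5 = 29.0, with 4 and 2(21−3) = 36 degrees of freedom. The between-visit correlation of 0.5 and full sphericity are assumed, since the article does not state them.
- Power is 0.990 at N = 21 and 0.973 at N = 18, so the stated 21 reproduces. It concerns one pain outcome.

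**2. Number of outcomes.** Two pain scores (Data collection and Outcomes measures both list usual and running pain), one function score, and 2 + 4 = 6 angles make nine. One is primary and eight are secondary.

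**3. Independent outcomes, all nulls true, each tested at 0.05.** The chance of at least one significant result among k tests is 1 − 0.95^k.
- k = 9: 1 − 0.95⁹ = 0.370
- k = 8 (secondaries): 1 − 0.95⁸ = 0.337
- k = 6 (angles): 1 − 0.95⁶ = 0.265

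**4. Correlated outcomes.** The documents give no between-outcome correlation, so a range is assumed. Two simulations were run with equally correlated outcomes under the null. One generated 10 runners per arm at three visits and used the F(4, 54) interaction test (6,000 replicates). The other used the large-sample 4-df version of that test (100,000 draws).

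| Assumed correlation | Nine outcomes, F test | Nine outcomes, large-sample | Six angles, large-sample |
|---|---|---|---|
| 0 | 0.375 | 0.371 | 0.267 |
| 0.2 | 0.344 | 0.353 | 0.256 |
| 0.5 | 0.275 | 0.285 | 0.215 |
| 0.8 | 0.178 | 0.177 | 0.149 |

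Against 0.05, the nine-outcome figure is 0.178/0.05 = 3.6 times as large at correlation 0.8 and 0.370/0.05 = 7.4 times as large under independence. The expected number of false positives does not depend on correlation: 9 × 0.05 = 0.45 over all outcomes, and 6 × 0.05 = 0.30 over the angles.

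**5. What the Sidak step does.** For three group pairs it tests each at 1 − 0.95^(1/3) = 0.0170, within one outcome's model. The number of outcomes does not enter, so the figures in steps 3 and 4 are unaffected.

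**6. The primary outcome.** A single fixed primary has an error rate of 0.05 however many secondaries follow. If either pain score could be claimed as primary, the rate could reach 1 − 0.95² = 0.0975 under independence.

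**The case against.** The strongest reply has four parts.

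- **A hierarchy of labels exists.** This stands. A reader might infer that the plan has no hierarchy at all, or that the trial's primary error rate is 37%. The documents do not support either: both the Abstract and the outcomes section name one primary and call function and kinematics secondary, and one fixed primary stays at 5%. What is missing is a rule tying the labels to the testing. The labels are also undercut by a primary objective that includes the secondaries.
- **Multiplicity for secondaries is commonly left to an analysis plan, and unadjusted secondaries beside one primary are accepted practice.** This would be decisive if the article were silent. It is not: it fixes the alpha, fixes the multiplicity method and limits it to pairs ("Sidak’s post-hoc will be used to make pairwise comparisons"). A later analysis plan could add an adjustment, but that would not take kinematics out of the published primary objective.
- **No one figure follows from the documents.** This stands. About 27% for nine outcomes needs an assumed correlation near 0.5. The supportable statement is a range. A higher figure could be had by assuming ungated Sidak comparisons at each later visit, but the article does not specify that procedure.
- **The event counted is not the stated hypothesis.** This also stands. A significant 4-df interaction test can reflect a difference between the two programs or a change in the wrong direction. The hypothesis needs both programs to beat control, on pain, symptoms and kinematics. A reader might take the figures as the false-positive rate of that whole hypothesis; they are not. That rate was not calculated and should be lower. Nor does the article say that one significant outcome will count as success; it only leaves that possible.

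**Conclusion.** The point holds in a limited form. The primary objective is wider than the primary outcome, and the stated error control does not reach across the nine outcomes it covers. With every null true, at least one significant group-by-time test among nine outcomes has a probability of about 37% under independence, 27–29% at a correlation of 0.5 and 18% at 0.8. For the six angles alone the figures are about 26%, 21% and 15%. They rest on equal correlation between outcomes, an assumed range for that correlation, and one interaction test per outcome at 0.05.

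The confirmatory result on a single primary pain outcome is not put in doubt by this, provided the article settles which pain score that is. What is in doubt is the standing of any isolated finding on function or an angle. The change is worth making because it alters what the trial may conclude and costs almost nothing.

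**What to change.** - **Abstract and Outcomes measures:** reconcile which pain score is primary.
- **Data analysis:** state that only this outcome is tested confirmatorily at 0.05. Report the other pain score, function and the six angles as supportive, with estimates and 95% confidence intervals. If claims on them are wanted, test them only after the primary succeeds, for example the other pain score, then function, each at 0.05 and only if the previous test succeeds, then the six angles with Holm adjustment (smallest p-value against 0.05/6 = 0.0083).
- **Introduction and Abstract:** reword the primary objective and the hypothesis so that function and kinematics are secondary.

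This takes a few sentences, with no new data or participants. The price is that an isolated significant angle or function score can no longer be claimed as confirmed.
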